##### Facial measurements

Prior to surgery, the laser operator will measure and record for each patient the distances between the corner of the eye and angle of the mandible, between the tragus and the lip commissure, and between the tragus and pogonion as described by Amarillas-Escobar *et al.*[15].

##### Mouth opening

Prior to surgery, mouth opening will be assessed by the laser operator, using a caliper to measure the distance between the incisal edges of the upper and lower central incisors as described previously [11,13,14,17].

### LLLT

#### Instrument

The Photon Laser III GaAlAs (DMC, São Carlos, São Paulo, Brazil) will be used. The active medium are a Arsenide-Gallium-Aluminium and a Indium-Gallium- Aluminium- Phosphide semiconductor diodes. Emission is in the red and near -infrared wavelengths, with variable power values in the continuous emission mode. The display provides the dosage according to the power and application time.

#### Irradiation parameters

The laser operator will perform the LLLT for each patient immediately following third molar surgery using the parameters given in Table 2.

**Table 2 T2:** LLLT parameters

**Parameter**	**Red laser**	**Infrared laser**
Center wavelength [nm]	652	808
Spectral bandwidth (FWHM) [nm]	5	2.6
Operating mode	Continuous wave	Continuous wave
Average radiant Power [mW]	100	100
Polarization	Random	Random
Aperture diameter [cm]	0.094	0.094
Irradiance at aperture [mW/cm^2^]	3537	3537
Beam profile	Multimode	Multimode
Beam spot size at target [cm^2^]	0.02827	0.02827
Irradiance at target [mW/cm^2^]	3537	3537
Exposure duration [s]	30	30
Radiant exposure [J/cm^2^]	106	106
Radiant energy [J]	3	3
Number of points irradiated	4	4
Area irradiated [cm^2^]	0.113	0.113
Application technique	Contact	Contact
Number and frequency of treatment sessions	1 session	1 session
Total radiant energy [J]	12	12

Intraoral irradiation will be performed by positioning the laser probe directly in contact with four points on the gingival mucosa in the area of the surgical field: point 1, – middle of the bone socket; 2, - the cervical third of the lingual face; 3, - the middle third of the lingual face; and 4 - apical third of the lingual face. The laser will be applied for 30 seconds for each point.

Extraoral irradiation will be performed by positioning the laser probe in contact with the skin on four points of the masseter muscle: 1 –, lower region (near the mandibular insertion); 2 –, lower middle region; 3 –, upper middle region; and 4 –, upper region (near the insertion of the zygomatic arch). Again, the laser will be applied for 30 seconds for each point.

#### Postoperative evaluations

##### Evaluation of postoperative pain

Because postoperative pain following third molar extraction reaches its maximum intensity within 3 to 5 hours, continues for 2 to 3 days and gradually decreases until the postoperative day 7, this outcome will be assessed 2 and 7 days following surgery [18] using a visual analog scale (VAS) and the Numeric Rating Scale 101 (NRS-101). The VAS is a 10 cm linear scale, ranging from 0 (no pain) to 10 (worst possible pain), while the NRS-101, measures pain on a scale ranging from 0 (no pain) and 100 (worst possible pain). The patients will be instructed by one of the post-surgical evaluators to mark a point on the VAS, indicating the intensity of the pain [12,15,22] and for the NRS-101, to attribute a number between 0 and 100 that best represents the pain they are experiencing [11,20].

##### Evaluation of postoperative swelling

Postoperative swelling reaches a peak 12 to 48 h following third molar extraction and begins to decrease during the subsequent days, disappearing around 5 to 7 days postoperatively [19,23,26,27]. To measure swelling, most authors measure the distance between two [11,13,14,23] or three predetermined anatomical points on the face [15]. In the present study, the same three evaluators mentioned above will measure the distances between the corner of the eye and angle of the mandible, between the tragus and lip commissure and between the tragus and pogonion of each patient 2 and 7 days following surgery.

##### Evaluation of postoperative muscle spasm

Spasms in the muscles of mastication can limit or even prevent mouth opening following surgical removal of impacted third molars [11-17]. This outcome is usually assessed by measuring the distance between the incisal edges of the upper and lower central incisors using a caliper [11,13,14,17]. In the present study, the same three evaluators will measure mouth opening in each patient at 2 and 7 days following surgery.

##### Evaluation of presence and intensity of hematoma/ecchymosis

The presence of hematoma/ecchymosis will be evaluated by measuring the largest diameter of any color changes in the skin of the cheek and submandibular region at 2 and 7 days after surgery. The measure will be performed by the same three evaluators, who will classify the occurrence of this outcome into four categories: 1) no color changes; 2) spot diameter of less than 4 cm; 3) spot diameter between 4 and 10 cm; and 4) spot diameter greater than 10 cm, as described by Bjornsson *et al*. [28].

##### OHIP-14 questionnaire

The 14-item Oral Health Impact Profile (OHIP-14) is a simplified form of the original OHIP questionnaire used for evaluating of the effect of oral health status on quality of life (QOL). The items are classified into the following subscales: functional limitation, pain, psychological discomfort, physical disability, psychological disability, social disability and handicap. The questionnaire will be administered to the patients by the same three evaluators 7 days following surgery.

##### Patients’ feelings concerning their postoperative status

The same three evaluators will ask the patients the following 10 questions at 2 and 7 days after surgery:

1) Are you maintaining your normal social activities?

2) Are you working/studying normally?

3) Are you maintaining your normal diet?

4) Have you had difficulty swallowing because of the surgery?

5) Have you had difficulty tasting foods?

6) Can you chew on the operated side?

7) Have you had trouble sleeping because of the surgery?

8) Have you had difficulty speaking because of the surgery?

9) Has your appearance changed because of the surgery?

10) Have you experienced nausea since the surgery?

### Evaluation of results

The patients will be evaluated 2 and 7 days after surgery with regard to the three primary outcomes: pain (VAS and NRS-101), swelling (comparison of preoperative and postoperative facial measurements) and muscle spasms (comparison of preoperative and postoperative mouth opening). The following data will also be recorded, as these are frequently analyzed in postoperative evaluations [1,15,24,25,29-33]: degree of surgical difficulty (Pell and Gregory classification, Winter classification and modified Prant classification); number of cartridges used for anesthesia; occurrence of hemorrhage during surgery; duration of surgery (minutes) from initial incision to final suture; and presence of hematoma/ecchymosis (largest diameter of color changes in the skin of the cheek and submandibular region). Individual variables (gender, ethnicity, educational level and age), OHIP-14 score and effect of surgery on QOL using the 10-item questionnaire will be evaluated, as suggested by other authors [29,31-36].

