### Study design and composition of study sample

The study design will consist of five treatments evaluated on two occasions (at 2 and 7 days following surgery). Table 1 shows the scheme for repeated-measures analysis of variance. Because the measures of pain, swelling and mouth opening have low variability when using the proposed scales, 40 degrees of freedom will be sufficient to control for residual variance. Thus, a minimum sample size of 50 subjects (10 in each group) is sufficient. Thus 50 patients undergoing treatment at the center for the removal of impacted lower third molars will participate in the study.

**Table 1 T1:** Scheme for repeated-measures analysis of variance

**Causes of variation**	**Degrees of freedom**
Treatment	4
Period	1
Treatment × period	4
Residual	40
Total	49

In addition, as this work predicts a two-factor (two wavelength), two-group (two irradiation sites) analysis, there will be 20 patients in each group (10 in each experimental subgroup) and 20 in control group. The power analysis (Figure 1) shows that for medium and large effect size, the test power will remain above 0.8 for 20 subjects in each group.

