### Statistical analysis

All data will be analyzed with respect to the normality of distribution using the Shapiro-Wilk test. Statistically significant differences between the experimental groups will be determined using analysis of variance, followed by a suitable post hoc test, if necessary. The significance level will be set at α = 0.05. By assuming normality in the distribution of the data, two-way ANOVA offers a high power for the design of this trial.

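### The three primary outcomes hold up to six measures at two visits, with no lead measure or visit and one undivided alpha of 0.05, so the chance of a false-positive primary result exceeds 5% on every reading (about 11 to 46%)

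*Protocol article*

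**What the plan says.** All places are in the protocol article.

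- **Evaluation of results** has patients evaluated at days 2 and 7 on "the three primary outcomes: pain (VAS and NRS-101), swelling (comparison of preoperative and postoperative facial measurements) and muscle spasms", the last judged by the change in mouth opening from before surgery.
- **Evaluation of postoperative pain** assesses pain "using a visual analog scale (VAS) and the Numeric Rating Scale 101 (NRS-101"). Neither scale is ranked above the other.
- **Evaluation of postoperative swelling** records three distances: "between the corner of the eye and angle of the mandible, between the tragus and lip commissure and between the tragus and pogonion". It does not say whether they are tested one by one or combined.
- **Study design and composition of study sample** describes "five treatments evaluated on two occasions (at 2 and 7 days following surgery"). Table 1 places both visits in one repeated-measures analysis of variance with treatment, period and treatment-by-period terms.
- **Statistical analysis** states: "The significance level will be set at α = 0.05". It plans analysis of variance and, where needed, a post hoc test that is not named. That test concerns differences between groups, not the number of outcomes.

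No section says how many of the three outcomes, or which measure or visit within each, must be positive for the trial to support laser therapy.

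**The concern.** When several results each carry primary status and each is judged at 0.05, the chance that at least one is significant by luck exceeds 0.05. Here the count is also left open: two pain scales, three distances that may or may not be combined, two visits, and two model terms that could each be read as a treatment finding. With nothing ranked, a claim of benefit could rest on whichever scale, distance or model term happened to reach significance, and it would still be reported as a primary outcome.

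Naming the primary measure and its time point belongs in the protocol. An unseen analysis plan might add an adjustment, but this article itself gives equal primary standing to both pain scales and both visits.

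**Working it through.** **The plan's own figure.** The article states no error rate across outcomes. Its only figure is 0.05 for a single test, which is the one-test case of the formula below: 1 − 0.95^1 = 0.05.

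**Inputs from the article.** Alpha is 0.05 (Statistical analysis). The measures number 2 + 3 + 1 = 6 (pain, swelling, mouth opening). There are 2 visits. Groups are 10, 10, 10, 10 and 20 (Randomization and composition of groups).

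**Assumed inputs.** The article gives no correlations. Five scenarios were used, from independence to very high correlation: between the two pain scales 0 to 0.95, between facial distances 0 to 0.8, across outcomes 0 to 0.7, and across visits 0 to 0.8.

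**Step 1: independent tests.** The chance of at least one false positive in k tests is 1 − 0.95^k.

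- k = 3: 1 − 0.95^3 = 0.143
- k = 4: 1 − 0.95^4 = 0.185
- k = 6: 1 − 0.95^6 = 0.265
- k = 12: 1 − 0.95^12 = 0.460

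**Step 2: correlated tests.** 20,000 trials per scenario were simulated with no treatment effect, normal data and the group sizes above. The five groups were compared by F test. The treatment term was tested on the average of the two visits and the treatment-by-period term on their difference.

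| Reading of the plan | Tests | Independence | Moderate correlation | Very high correlation |
|---|---|---|---|---|
| One measure per outcome, treatment term only | 3 | 14.4% | 13.9% | 11.2% |
| Swelling combined, both pain scales, treatment term only | 4 | 18.5% | 15.9% | 12.3% |
| Six measures, treatment term only | 6 | 26.7% | 22.4% | 16.2% |
| Six measures, treatment and treatment-by-period terms | 12 | 45.9% | 39.8% | 30.2% |

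The independence column agrees with Step 1 to within simulation error. The lowest value, 11.2%, is still more than twice 5%. Post hoc comparisons among the five groups are not counted.

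**Step 3: effect of Holm.** With three primary tests, the successive thresholds are 0.05/3 = 0.0167, 0.05/2 = 0.025 and 0.05. This holds the error across the three at or below 5% whatever their correlation.

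**Step 4: cost of the stricter threshold.** Take all laser arms pooled (40) against control (20) as an illustration. The standard error of the standardised difference is sqrt(1/40 + 1/20) = 0.274. The difference detectable with 80% power in a two-sided t test on 58 degrees of freedom is 0.78 at alpha 0.05 and 0.91 at alpha 0.0167.

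**The case against.** **Twelve separate tests at 0.05.** A reader might infer that each of six measures is tested on its own at each visit, and quote 46% as the error rate. The text does not support that. Table 1 puts both visits in one model, and nothing says the three distances are tested separately; Evaluation of results lists swelling as one outcome. The 46% also requires full independence, which is implausible for two pain scales and repeat visits in the same patients. This objection stands, and it is why the result is a range by reading.

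**Dilution of a day-2 effect.** A reader might also infer that giving day 7 equal weight hides an early effect. Suppose the day-7 effect is zero and the between-visit correlation is 0.5. The averaged effect is then 0.5/sqrt((1 + 0.5)/2) = 0.58 of the day-2 effect, and power for a difference of 0.8 at 40 against 20 falls from 0.82 to 0.38. That is true of the treatment term alone. The planned treatment-by-period term works on the visit difference, whose standard deviation under the same assumptions is sqrt(2(1 − 0.5)) = 1. It therefore sees the full 0.8, with power of about 0.82. The dilution claim cannot be sustained.

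**Three separate questions.** The Background poses pain, swelling and muscle spasm as distinct effects, so control across the three can be debated, and adjustment is often left to an analysis plan. This has some force for the choice of method. It does not explain why two pain scales and two visits share primary status within one outcome.

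**Conclusion.** The concern holds in a limited form. The article fixes three primary outcomes containing up to six measures at two visits, names no lead measure or visit, and sets one alpha of 0.05 with no control across them. The chance of at least one false-positive primary result is:

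- about 11 to 14% with one treatment test per outcome;
- 12 to 19% if swelling is combined and both pain scales are tested;
- 16 to 27% for the treatment term on six measures;
- 30 to 46% if treatment and treatment-by-period both count for six measures.

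Where the figure falls depends on correlations that the article does not give and on a reading that it leaves open. That it exceeds 5% holds on every reading and in every correlation scenario examined. No loss of power from averaging the visits is claimed.

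**What to change.** Before unblinding, while data are still being collected (Trial status), add the following to the protocol or analysis plan:

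1. One measure per outcome: one of the two pain scales (the sponsor's choice, since the article favours neither), one combined swelling measure such as the mean percentage change of the three distances, and mouth opening.
2. One primary visit. Day 2 is best supported: the article describes swelling as "disappearing around 5 to 7 days postoperatively" and pain as declining up to day 7. It gives no time course for mouth opening.
3. The single test that decides each outcome, with Holm across the three.
4. The other pain scale, the single distances and the other visit as secondary.

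The change is wording only. Its price is the 0.0167 threshold at the first Holm step, so the detectable effect rises somewhat. The 0.78 to 0.91 illustration rests on a pooled laser-against-control contrast that the protocol does not state; the figure should be recalculated for the contrast the sponsor chooses.

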### Randomization and composition of groups

After undergoing a clinical evaluation by the dental surgeons, patients who meet the eligibility criteria will be divided into five experimental groups (Figure 2) based on a randomization method involving raffle numbers. Randomization will be conducted by a researcher not involved in the recruitment and treatment of the participants. Concealed allocation will be performed using a set of random numbers placed in sealed opaque envelopes. The laser operator will open the envelope containing the procedure to be performed on each patient immediately following third molar surgery. Sealed envelopes awaiting new subjects will be kept in a safe place and given to the operator as the sessions are scheduled. The 40 patients will be allocated into four experimental groups or a control group as follows: Group 1 (660 nm laser, applied intraorally, n = 10), Group 2 (808 nm laser, applied intraorally, n = 10), Group 3 (660 nm laser, applied extraorally, n = 10), Group 4 (808 nm laser, applied extraorally, n = 10), Group 5 (control; no irradiation, n = 20).

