### Blinding procedures

The surgical procedures will be performed by two dental surgeons and a third person will perform both the preoperative evaluation and LLLT. Following a calibration exercise, three blinded examiners, who have not previously been involved in the evaluation, surgery or laser therapy, will perform the postoperative evaluations. The patients will be unaware of the group to which they are allocated.

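### Swelling and mouth opening: the named ANOVA has no baseline term, although adjusting for the preoperative value already collected would usually be more precise

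*Protocol article*

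**What the plan says.** The protocol article has the laser operator record three facial distances and mouth opening before surgery (sections Facial measurements and Mouth opening). Evaluation of results then defines two of the three primary outcomes from these readings: "swelling (comparison of preoperative and postoperative facial measurements) and muscle spasms (comparison of preoperative and postoperative mouth opening"). It does not say whether the comparison is a difference, a percentage or something else.

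The Statistical analysis section states that "Statistically significant differences between the experimental groups will be determined using analysis of variance", followed by a post hoc test if needed, and refers to a two-way ANOVA as giving high power. Table 1 lists treatment, period, treatment by period and residual. The two periods are days 2 and 7, so the preoperative reading is neither a level of period nor a covariate.

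On timing, Randomization and composition of groups says: "The laser operator will open the envelope containing the procedure to be performed on each patient immediately following third molar surgery". The preoperative values therefore precede knowledge of allocation.

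**The concern.** A between-group ANOVA applied to a pre/post comparison is most naturally read as an analysis of change. A change score uses the baseline with a fixed slope of 1. Analysis of covariance (ANCOVA) estimates that slope. If the true slope is below 1, the change score over-corrects for baseline and carries avoidable variance.

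What is at stake is precision on two of the three primary outcomes, in laser arms of 10 patients. Pain has no preoperative reading and is not affected. The article defends its model on grounds of power, so a more powerful use of data already being collected is a fair point to raise.

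**Working it through.** **Inputs.** Alpha: "The significance level will be set at α = 0.05" (taken as two-sided). Arm sizes: four laser arms of 10, and "Group 5 (control; no irradiation, n = 20"), so 60 in all. Elsewhere the article gives 50 or 40 patients; the arm sizes in the randomization section are used here. The article gives no SD, effect size in figures or correlation r, so r is varied from 0.3 to 0.95 and the effect is assumed.

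**The plan's own power figure.** The article says that "for medium and large effect size, the test power will remain above 0.8 for 20 subjects in each group", and that "there will be 20 patients in each group (10 in each experimental subgroup) and 20 in control group". It does not name the test. Take Cohen's f = 0.25 (medium) and 0.40 (large) as assumptions. A one-way ANOVA on 3 x 20 has noncentrality f² x 60 = 3.75 and 9.6 on 2 and 57 df, which gives power 0.37 and 0.78. A group-by-period test on 3 x 20 with an assumed within-patient correlation of 0.5 gives 0.93 for the medium effect. The statement can therefore be met for an interaction but not for this between-group test at a medium effect. Figure 1 is not available, so this cannot be settled. The figure makes no visible use of baseline and does not bear on what follows.

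**Variance of the two analyses**, for one postoperative occasion, with preoperative SD s0 and postoperative SD s1:

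- Change: s0² + s1² − 2·r·s0·s1
- ANCOVA with known slope: s1²(1 − r²)
- Change minus ANCOVA: (s0 − r·s1)², which is never negative

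With s0 = s1 = s, change is 2s²(1 − r), ANCOVA is s²(1 − r²), and the ratio is (1 + r)/2.

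| r (assumed) | ANCOVA / change | Patients under ANCOVA matching 60 under change |
|---|---|---|
| 0.3 | 0.65 | 39 |
| 0.5 | 0.75 | 45 |
| 0.7 | 0.85 | 51 |
| 0.9 | 0.95 | 57 |
| 0.95 | 0.975 | 58.5 |

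**Price of estimating the slope.** With 60 patients, five arms and one covariate, the residual df are 60 − 5 − 1 = 54. The expected variance is multiplied by about 1 + 1/53 = 1.019. Break-even is (1 + r)/2 x 1.019 = 1, which gives r of about 0.96.

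**Power**, for an assumed effect of 0.8 SD of change, by noncentral t, with one df less for ANCOVA. For one laser arm v control (10 v 20), the noncentrality for change is 0.8/√(1/10 + 1/20) = 2.066 on 28 df. ANCOVA divides the noncentrality by √((1+r)/2).

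| Comparison | Change | r = 0.3 | r = 0.5 | r = 0.7 | r = 0.9 |
|---|---|---|---|---|---|
| 10 v 20 | 0.51 | 0.69 | 0.63 | 0.58 | 0.53 |
| 10 v 10 | 0.40 | 0.55 | 0.50 | 0.45 | 0.41 |

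**Where the gain falls.** It applies to treatment differences at day 2, at day 7 or over both days. In the treatment-by-period contrast the baseline already cancels from a change score, so a common baseline slope adds nothing there.

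**The case against.** The strongest reply is that the article does not fix a change score. It says only that pre- and postoperative values are compared, it excludes no covariate, and the way baseline enters a model is often left to an analysis plan, which is not shown here. This stands as a limit on the point: the reading as change is natural but is an inference. It does not remove the point, because the article names its model, lists its sources of variation in Table 1 and defends the choice on power, all without a baseline term.

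It also stands that ANOVA of change is a valid analysis in a randomised trial, that the size of the gain depends on an unstated r, and that at a high r there is almost nothing to win.

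A reader might infer more, but the documents do not support it:

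- **Different readers cost precision.** The article says that "a third person will perform both the preoperative evaluation and LLLT", while three other examiners read days 2 and 7. One person reads every baseline, so a constant offset is common to all arms and cancels between them. Extra noise from differing examiners would need them to share out the patients and to differ systematically. The article does not say so; its wording suggests that all three measure each patient, after a calibration exercise. No figure for added variance can be drawn from it.
- **The baseline reader should be changed for remaining patients.** Data collection has begun (Trial status). A change now would mix readers across patients and could create the noise it was meant to remove.
- **Surgical difficulty, duration and surgeon must enter the model.** These are debatable additions in arms of 10. The article also does not say that the difficulty grade is recorded before the envelope is opened.
- **The analysis is biased.** Baseline is read before allocation is known and all arms share the same readers. Nothing here points to bias or an inflated type I error rate.

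**Conclusion.** The point holds as one of efficiency. The preoperative value is collected but, in the analysis named, is used only through the pre/post comparison. Replacing this with covariate adjustment would cut residual variance by about 35% at r = 0.3, 25% at 0.5, 15% at 0.7 and 5% at 0.9, before the small cost of estimating the slope. The gain disappears near r = 0.96.

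The percentages rest on three assumptions: that the comparison is a simple difference, that pre- and postoperative variances are equal, and that r lies in the range shown. The power figures add an assumed effect of 0.8 SD of change and illustrate the gain only; they do not estimate this trial's power. Because the cost is so small, the change is worth making even though r is unknown.

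**What to change.** State in the Statistical analysis section, before outcome data are compared by arm, that the day 2 and day 7 facial distances and mouth opening will be analysed in the repeated-measures model with treatment, period and treatment by period, and with the corresponding preoperative value as covariate. Swelling and loss of opening can still be reported descriptively as differences from baseline. If the full analysis plan already does this, the article's wording and Table 1 need only be brought into line.

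The cost is one degree of freedom per outcome and one sentence of text. No new measurement, staff or patients are needed, and the current readers stay as they are.
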